# Benefit of glucosyl Hesperidin in patients with primary biliary cholangitis: A multicenter, open-label, randomized control study

**DOI:** 10.1097/MD.0000000000032127

**Published:** 2022-12-02

**Keywords:** gamma-glutamyl transferase, glucosyl hesperidin, nuclear factor erythroid 2-related factor 2, oxidative stress, primary biliary cholangitis

## Abstract

**Methods::**

Patients with PBC who are 20 years or older will be eligible to participate. Patients will be assigned to 1 of 2 groups and given either 500 or 1000 mg of glucosyl hesperidin per day. The primary endpoint is the ratio of changes in serum gamma-glutamyl transferase levels before and after 24 weeks of glucosyl hesperidin administration. The secondary endpoints are serum hepatobiliary enzyme levels (alkaline phosphatase, transaminase, and total bilirubin levels) and the protein expression levels of nuclear factor erythroid 2-related factor 2 and its target molecule 8, 16, and 24 weeks after administration compared to before administration.

**Discussion::**

The prospective clinical interventional study was designed to assess the supportive effect of glucosyl hesperidin on hepatic function in patients with PBC receiving basic ursodeoxycholic acid treatment.

## 1. Introduction

In Japan, the number of patients with chronic liver disease has risen to 9 million for chronic hepatitis and 0.4 to 0.5 million for liver cirrhosis.^[1]^ The etiology of liver cirrhosis is changing, owing primarily to the establishment of chronic hepatitis C treatment, and the proportion of non-viral liver diseases is actually increasing. In fact, the number of patients with autoimmune hepatitis and/or primary biliary cholangitis (PBC) has more than tripled in the last decade.^[2]^ Even though treatments for viral hepatitis have made significant progress, the pathophysiology of autoimmune hepatitis and PBC remains unknown, and no curative treatment has been established.

Growing evidence suggests that oxidative stress plays a significant role in the pathogenesis of chronic liver disease regardless of the cause of liver damage.^[3–7]^ Furthermore, in patients with PBC, a mechanism that impairs antioxidant activity via the nuclear factor erythroid 2-related factor 2 (Nrf2)/Kelch-like ECH-associated protein 1 pathway was reported.^[8]^ However, it is unknown whether activating the Nrf2/Keap1 pathway improves PBC pathology.

Ursodeoxycholic acid (UDCA) is widely used as a basic therapeutic agent for PBC and has been reported to promote hepatic Nrf2 activation and reduce oxidative stress.^[9]^ However, because intact enterohepatic circulation is required for its medicinal effect, its effect is significantly attenuated in the pathological condition in which cholestasis has progressed when compared to the early stage of the disease.^[10]^ Previous research has shown that oxidative stress is an independent predictor of stage progression in patients with PBC^[11]^ and that antioxidant levels of vitamins A, C, and E are significantly lower.^[12]^ Taking these facts into account, Nrf2 activation was linked to an improvement in the pathological condition of PBC.

Glucosyl hesperidin is a type of water-soluble polyphenol with high component stability among antioxidants, and its effect is expected to be sufficient. It has been certified by Japanese Agricultural Standards as a safe anti-whitening agent for canned oranges or orange juice. Glucosyl hesperidin is a water-soluble derivative of hesperidin, and hesperidin was found in sera hydrolyzed with beta-glucuronidase after the oral administration of glucosyl hesperidin.^[13]^ Serum hesperidin levels increase in a dose-dependent manner without causing any adverse events (AEs), and human blood levels have been reported to be approximately 12 µM in the case of a 3000 mg oral intake.^[14]^ In this study, hesperidin was effective when administered with standard anti-rheumatoid therapy in ameliorating rheumatoid arthritis in mice and humans without any adverse effects. In a rat study, hesperidin oral administration resulted in concentration-dependent activation of Nrf2 in the liver and improvement of the inflammatory index.^[15]^ Additionally, organ protective effects of hesperidin on liver and spleen were also rereported.^[16–18]^

By the way, there have been many reports which show that improvement over time in biochemical test values such as serum gamma-glutamyl transferase (GGT) and alkaline phosphatase after medical therapy intervention is very useful as a better indicator of long-term life prognosis in patients with PBC.^[19–22]^

Based on these evidences, the potential of glucosyl hesperidin as a therapeutic agent for PBC will be investigated in this study through antioxidative stress mechanisms by evaluating the improvements of hepatic biochemical indicis including GGT and alkaline phosphatase.

## 2. Methods

### 2.1. Design

This is a multicenter, open-label, randomized, parallel-group study comparing the influence of glucosyl hesperidin on liver function with UDCA treatment in patients with PBC (Fig. 1). Patients aged 20 years or older are eligible to participate. The inclusion and exclusion criteria are listed in Table 1. Patients will be randomly assigned to either the 500 mg/day or 1000 mg/day treatment groups. In these treatment groups, either 500 mg or 1000 mg of glucosyl hesperidin will be given orally once per day for 24 weeks in addition to ongoing UDCA treatment.

**Table 1 T1:** Inclusion and exclusion criteria.

Inclusion criteria
1.Primary biliary cholangitis.
2.Be at least 20 years old at the time of consent acquisition.
3.Patients with a performance status ECOG of 0 or 1.
4.Patients with no dose changes for UDCA and fibrate.
5.Patients who were adequately informed about the study’s objectives and voluntarily provided written consent by themselves or their surrogate.
Exclusion criteria
1.Patients with hesperidin hypersensitivity.
2.Patients who routinely consume hesperidin-containing health foods prior to participating in this study.
3.Patients scheduled for or undergoing treatment for malignant tumors.
4.Patients with a NYHA functional classification of 2 or higher.
5.Patients who experience dyspnea during daily exertion.
6.Patients with a total bilirubin level of 3.0 mg/dL or higher, or a Child-Pugh classification of B or C.
7.Patients with an eGFR of less than 30 mL/minute/1.73 m^2^.
8.Patients who are or may become pregnant.
9.Patients who participated in other clinical trials within 3 months before starting hesperidin administration.
10.Patients deemed unsuitable by doctors to participate as research subjects.

ECOG = Eastern cooperative oncology group, eGFR = estimated glomerular filtration rate, NYHA = New York heart association, UDCA = ursodeoxycholic acid.

**Figure 1. F1:**
[figure not shown]
Study design. A total of 110 patients with PBC (55 in each group) will participate in this study. Following eligibility confirmation, patients will be randomly assigned to either the hesperidin 500 mg or 1000 mg treatment groups by an envelope method.

This study will be carried out in accordance with the Helsinki declaration (revised in October 2013) and the Clinical Trials Act of the Japanese Ministry of Health, Labour, and Welfare. The investigator will provide each patient with a thorough explanation of the study and will obtain written informed consent. The study protocol was approved by a certified ethics committee. The research will last from March 30, 2022, to March 31, 2024. The study’s organization is shown in jRCTs051210210.

### 2.2. Randomization

The study participants will be registered and allocated using stratified permuted block randomization. Participants will be randomly assigned to either the 500 mg/day or 1000 mg/day groups based on the following factors: registered facility and patient sex. Table 2 provides an overview of all visit and test schedules.

**Table 2 T2:** An overview of observation, clinical examination, and evaluation.

	Screening within 1 month	Obtaining informed consent within 1 month	Observation period					
			Treatment start date	8 weeks	16 weeks	24 weeks	36 weeks	At the time of discontinuation
Permissible range (weeks)				±2	±2	±2	±4	
Visits		1^st^	2^nd^	3rd	4th	5th	6th	
Allocation		✓						
Patient’s characteristics	✓	✓						
Treatment								
Adherence check			✓	✓	✓	✓		
Subjective symptoms	✓	✓	✓	✓	✓	✓	✓	✓
Adverse events			✓	✓	✓	✓	✓	✓
Blood examination			✓^*1^	✓	✓	✓	✓	✓^*2^

✓ means the day for each event in left column. *1: This examination can be omitted if a blood test is performed during the screening period or consent is obtained. *2: This examination can be omitted if patient consent cannot be obtained.

AEs = adverse events.

### 2.3. Endpoints

The primary endpoint is the rate of change in serum GGT levels from 0 to 24 weeks after glucosyl hesperidin administration. AEs will be collected for safety analysis. Any unfavorable or unexpected sign, symptom, or disease, including abnormal laboratory results, is considered an AE. Patients who have had their safety evaluation data collected after the start of study treatment will be included in the safety analysis set. The full analysis set and per-protocol set will be used to assess efficacy. The full analysis set is defined as the patient population that was excluded from the safety analysis set for any of the following reasons: ineligible cases after enrollment; and cases with no efficacy data at any time after the start of study treatment.

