### 2.4. Sample size

Since PBC, the study’s target disease, is a rare disease, the total number of participants in the study’s participating facility is expected to be around 110, and it is estimated to be 100 after the dropout. The difference between the treatment groups (standard and high dose administration groups) from the start (0 weeks) to the end of administration (24 weeks) is 5%, and the standard deviation is 5%. With a 7.5% probability, a power of 90% can be obtained at a significance level (both sides) of 5%.

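### The full analysis set is defined the wrong way round, as the patients removed rather than those who remain, and the wording conflicts with the safety set definition

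*Protocol article*

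**What the plan says.** Section 2.3 (Endpoints) of the protocol article deals with three analysis populations in consecutive sentences.

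- Safety set: "Patients who have had their safety evaluation data collected after the start of study treatment will be included in the safety analysis set".
- Efficacy populations: "The full analysis set and per-protocol set will be used to assess efficacy".
- Full analysis set (FAS): "The full analysis set is defined as the patient population that was excluded from the safety analysis set for any of the following reasons", and the reasons are "ineligible cases after enrollment; and cases with no efficacy data at any time after the start of study treatment".

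Section 2.5.2 specifies an unpaired t test on the relative change in GGT from week 0 to week 24, but does not name the set it is run on. Sections 2.5.3 and 2.5.4 do not name one either. No other part of the article restates or corrects the FAS definition.

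**The concern.** An efficacy population should be what is left after unusable cases are taken out. The printed sentence makes the FAS the cases taken out. It also refers to exclusions from the safety set that the safety set definition does not make.

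The stake is prespecification. This is the only definition of the FAS in the article, and a reader cannot check a reported FAS against a definition that yields no usable set. Whoever runs the analysis must replace the rule with an unwritten one, in an open-label trial where arms and GGT results are visible.

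A smaller matter follows once the sentence is turned round. The rule then removes patients found ineligible after enrolment. Members of the safety set have already been allocated and treated, so any such removal happens after randomisation with the arm unmasked. The sentence does not confine it to facts that were fixed before allocation.

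**Working it through.** The article gives no figure for this point, so there is none to reproduce. The check is one of set logic.

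**Inputs, all from section 2.3**

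- S: the safety set. The only condition for entry is safety data collected once treatment has started.
- I: patients found ineligible after enrolment.
- N: patients with no efficacy data at any point once treatment has started.

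**Step 1: strict reading.** The FAS is the set of patients excluded from S because of I or N. The definition of S mentions neither ineligibility nor efficacy data, so nobody is excluded from S for those reasons. The FAS is then the empty set.

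**Step 2: looser reading.** Suppose the sentence points to the safety set patients who meet either reason: FAS = S ∩ (I ∪ N). The section 2.5.2 endpoint is (GGT at week 24 − GGT at week 0) / GGT at week 0. Patients in N have no week 24 value, so they have no endpoint and cannot enter the t test. What remains is at most the ineligible patients who have a week 24 GGT. That is not a population in which anyone would choose to estimate the effect.

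**Step 3: probable intent.** FAS = S minus (I ∪ N). The sets in steps 2 and 3 do not overlap and together make up S. The printed rule on its looser reading is therefore the exact complement, within the safety set, of the rule that was probably meant.

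**Step 4: can the number affected be derived?** The Figure 1 legend says "A total of 110 patients with PBC (55 in each group) will participate in this study", and section 2.4 says of the total that "it is estimated to be 100 after the dropout". The difference is 110 − 100 = 10, but this is expected dropout, which is not the same as I ∪ N:

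- A patient who leaves after the week 8 blood test has efficacy data, so is not in N.
- A patient who completes week 24 may still be found ineligible, so can be in I.

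The size of I ∪ N could be below or above 10, and the article does not give it.

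**Step 5: what the intended reading leaves open.** The Figure 1 legend places confirmation of eligibility before randomisation, so removal for ineligibility after enrolment concerns patients who had passed that check. Table 2 places allocation at the first visit and ticks the blood examination at the second, the treatment start date; a footnote lets an earlier test stand in for it. A bilirubin or eGFR value that bears on the Table 1 criteria can therefore be dated after allocation. The last exclusion criterion in Table 1 rests on a doctor's judgement. Nothing says these are used to remove patients later, but the printed rule does not rule it out.

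**The case against.** The strongest reply is that nobody would analyse the complement. A literal reading that gives an empty set signals a slip of wording or translation, and the two listed reasons make the intent plain. That stands. A reader might infer that the efficacy analysis will really be run on ineligible and no-data patients; the article does not support that as an expectation. What survives is that the stated rule is wrong and is not corrected elsewhere.

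Three further objections also stand, and they limit the point:

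- A reader might infer that the FAS carries the primary analysis. The article says only that the FAS and the per-protocol set are both used for efficacy.
- A reader might take the comparison to be about 10 patients against about 100. Step 4 shows that those figures describe dropout.
- A reader might infer that staff who know the arm and the GGT results are meant to remove patients at their discretion. The doctor's-judgement item is an entry criterion, and eligibility is confirmed before randomisation. Procedures for judging eligibility are commonly left to a full protocol or analysis plan, which is not shown. Arm-aware removal is a risk that the wording allows, not a stated rule, and its absence from a condensed article would not be a finding by itself.

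The last objection does not make a limit on removals pointless. The sentence has to be rewritten anyway, and the rewritten version will state a post-randomisation exclusion in an open-label trial.

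**Conclusion.** The FAS definition is wrong as written and inconsistent with the safety set definition beside it. Followed literally, it gives an empty set (strict reading) or one confined to patients unfit for the efficacy comparison (looser reading). This rests on the printed wording alone and needs no numerical assumption.

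That the intended set is the safety set minus the two groups is an inference, though a strong one. The number of patients affected cannot be stated, and no bias in the eventual result is shown. The consequence applies to the FAS analyses, whichever efficacy set turns out to be primary. The error is in a stated analysis rule and should be corrected, but it does not touch the design, the sample size or the treatment.

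**What to change.** Replace the sentence in section 2.3 with wording such as:

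> The FAS is the safety analysis set after removing (a) patients found ineligible after enrolment and (b) patients without any efficacy measurement once study treatment has begun. Patients are analysed in the group to which they were allocated.

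Because the trial is open-label, add a limit on (a):

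> A patient is removed as ineligible only for an entry-criterion violation shown by data recorded before allocation, and the decision is made without reference to arm or outcome.

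The same correction is a natural place to say which efficacy set is primary, since the article leaves this open. The rewording keeps the plan's own test for having efficacy data. It does not settle how a patient with an early GGT value but none at week 24 is handled, which is a separate matter.

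The cost is a short correction to the published text and the corresponding line in any analysis plan. The small downside of the limit on (a) is that a few protocol violators stay in the FAS.

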#### 2.5.2. Primary endpoint.

The average “rate of change of biliary enzyme levels (serum GGT levels) at 24 weeks after glucosyl hesperidin administration from before administration (0 weeks)” will be compared between groups using an unpaired Student’s *t* test. In addition, the point estimate of the difference between the groups and the 95% confidence interval will be calculated.

The rate of change will be calculated as follows: serum GGT level (24 weeks)-serum GGT level (0 weeks)/serum GGT level (0 weeks).

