#### 2.5.3. Secondary endpoint.

For each item, the mean values for each group will be compared between groups using an unpaired Student’s *t* test. In addition, the point estimate of the difference between the groups and the 95% confidence interval will be calculated. The rate of change will be calculated as follows: each evaluation item (at each evaluation point other than 0 weeks) – each evaluation item (0 weeks)/each evaluation item (0 weeks). The following items will be included: Rate of change in biliary enzyme levels (serum GGT level) after glucosyl hesperidin administration (8 and 16 weeks) from before administration (0 weeks); rate of change in hepatobiliary enzyme levels (serum alkaline phosphatase, transaminase, and total bilirubin levels) after glucosyl hesperidin administration (8, 16, and 24 weeks) from before administration (0 weeks); and rate of change in Nrf2 protein expression levels and its target gene (HMOX-1) after glucosyl hesperidin administration (8, 16, and 24 weeks) from before administration (0 weeks).

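### The full analysis set admits patients without a week-24 GGT, but the primary t test cannot use them without imputation, so unequal, response-related dropout can bias the dose comparison

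*Protocol article*

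**What the plan says.** All references are to the protocol article.

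- **Analysis sets (section 2.3).** "The full analysis set and per-protocol set will be used to assess efficacy". The full analysis set is defined by two reasons: ineligibility found after enrolment, and "cases with no efficacy data at any time after the start of study treatment". Read literally, the sentence is inverted, because it makes the set consist of the patients excluded from the safety set. The evident intent is the safety set minus those two groups.
- **Primary endpoint and test (sections 2.3 and 2.5.2).** The variable is the GGT change "at 24 weeks after glucosyl hesperidin administration from before administration (0 weeks"), and the group means "will be compared between groups using an unpaired Student’s *t* test". The formula is "serum GGT level (24 weeks)-serum GGT level (0 weeks)/serum GGT level (0 weeks"), with brackets missing around the difference. It needs a week-24 value.
- **Interim GGT (section 2.5.3, Table 2).** Blood is taken at weeks 8 and 16. GGT change "after glucosyl hesperidin administration (8 and 16 weeks) from before administration (0 weeks") is a secondary endpoint, compared by t tests. A blood test at discontinuation is also scheduled, but may be omitted without patient consent.
- **Dropout (section 2.4).** The number of participants "is expected to be around 110, and it is estimated to be 100 after the dropout".
- **Design (sections 2.1 and 2.5.7).** The trial is open-label, and each facility's own laboratory measures GGT.

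**The concern.** The population and the test do not fit together. The population rule admits a patient on the strength of any efficacy value after treatment starts, while the test accepts only patients with a week-24 value. Taken as written, the primary test on the full analysis set shrinks to the patients who have a week-24 GGT.

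This matters because dose is known to patient and physician, and local GGT results are available during treatment. It is plausible, though not shown, that patients whose GGT rises early are more likely to leave, and that this happens more at one dose than the other. The remaining patients would then look better in the arm that lost more poor responders. The interim values that could correct for this are already scheduled, but an unpaired t test on week-24 change has no place for them.

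**Working it through.** **1. The plan's own figure.** Inputs from section 2.4: difference 5 points, two-sided alpha 5%, power 90%, 100 patients after dropout (50 per arm). The stated SD is 5%, and the next sentence contains an unexplained 7.5%.

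- SD 5: SE = 5 × √(2/50) = 1.0. Power = Φ(5/1.0 − 1.96) = Φ(3.04) = 99.9%.
- SD 7.5: SE = 7.5 × √(2/50) = 1.5. Power = Φ(5/1.5 − 1.96) = Φ(1.37) = 91.5% (91.0% with the noncentral t).

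The 90% is reproduced only if 7.5% is the SD and 50 per arm are analysed. The sizing thus appears to count patients remaining after dropout, and losing the other 10 costs no planned power. SD 7.5 is used below.

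**2. Bias formula.** Take 55 per arm, no true difference and correlation r between week-8 and week-24 change. Suppose the k patients with the largest week-8 rises leave an arm. That arm's observed week-24 mean then shifts by about

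−r × 7.5 × [k/(55 − k)] × m(k),

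where m(k) is the standard normal mean of the top k/55. The bias is the 1000 mg shift minus the 500 mg shift. A negative value favours 1000 mg, and the sign flips if 500 mg loses more.

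- 8 vs 2: (8/47) × 1.57 − (2/53) × 2.19 = 0.267 − 0.083 = 0.184. Times 7.5r: −0.69 (r = 0.5), −0.97 (r = 0.7).
- 6 vs 4: (6/49) × 1.71 − (4/51) × 1.90 = 0.210 − 0.149 = 0.061. Bias −0.23, −0.32.
- 10 vs 0: (10/45) × 1.45 = 0.323. Bias −1.21, −1.69.
- 5 vs 5: 0.

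**3. Simulation of the observed-case t test** (5,000 to 6,000 trials per scenario). The split, mechanism and correlation are assumptions; the documents give none of them.

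| Dropouts, 1000 mg : 500 mg | Who leaves (same rule in both arms) | Bias, r = 0.5 | Bias, r = 0.7 | Type I error |
|---|---|---|---|---|
| 5:5 or 8:2 | random | 0 | 0 | about 5% |
| 5:5 | largest week-8 rises | 0 | 0 | about 5–7% |
| 6:4 | largest week-8 rises | −0.2 | −0.3 | about 5–7% |
| 8:2 | more likely with a larger rise (weight × e per SD) | −0.4 | −0.5 | about 6–7% |
| 8:2 | largest week-8 rises | −0.7 | −1.0 | about 8–12% |
| 10:0 | largest week-8 rises | −1.2 | −1.7 | about 13–21% |

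An 8:2 variant in which dropout follows week-16 change plus noise gives −0.6 to −0.8 points and 7 to 10%.

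**4. Using the interim values.** Regressing week 24 on the earlier visit or visits within each arm, which is the likelihood estimate for this dropout pattern, brings the bias to about 0 in every scenario. With random dropout it lowers the standard error by only about 1 to 2%.

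**The case against.** The strongest reply is that this is only an unstated missing-data rule. The article nowhere says that only patients with a week-24 value are analysed, a t test is compatible with imputation, and a condensed article commonly leaves such rules to the full protocol or SAP. That stands in part: restriction to observed cases is inferred from the formula, and the absence of an imputation rule is not the finding. What remains is that the article itself fixes the test, variable, time point and population, and that test cannot by itself use weeks 8 and 16.

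Three stronger readings are tempting and unsupported.

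- **That the interim data are thrown away.** They are analysed as secondary endpoints, and a discontinuation sample is scheduled. They simply do not enter the primary comparison.
- **That the result will be biased.** Both arms receive the same product at different doses, and the documents give no dropout reasons or split. Random or symmetric dropout gives no bias.
- **That false positives near 17% should be expected at 8:2, or near 10% even at 5:5.** Those figures arise only if one arm loses its worst early responders while the other loses patients at random. With one mechanism in both arms they fall to 6 to 12% and about 5 to 7%.

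One could also say that a mixed model at 9% dropout is a matter of taste. The gain is indeed small if dropout is random. The case for the model is protection against the unequal case at almost no cost.

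**Conclusion.** The point holds in this limited form: the intended full analysis set is wider than the set the primary test can use, and the test leaves out information that would guard against response-related dropout. About 10/110 = 9% of patients are affected. Against the 5-point planning difference, the possible bias is nil under random or symmetric dropout, about 4 to 6% of it at 6:4 (0.2 to 0.3 points), 8 to 20% at 8:2 (0.4 to 1.0 points), and at most about a third in the extreme 10:0 case (1.7 points).

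These sizes rest on SD 7.5, correlation 0.5 to 0.7 and dropout driven by observed GGT. Dropout driven by unobserved values would not be fully corrected by the proposed model either. Planned power is not at issue. The change is worth making because it is cheap, not because bias has been shown.

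**What to change.** 1. Correct the inverted sentence in section 2.3 so that the full analysis set is the safety set minus ineligible patients and those without efficacy data after treatment start.
2. In section 2.5.2, make the primary full-analysis-set analysis a repeated-measures model of the GGT rate of change at weeks 8, 16 and 24. Include treatment, visit, treatment-by-visit, baseline GGT and the randomisation factors (facility and sex). The week-24 treatment contrast is primary, with its 95% confidence interval.
3. Keep the observed-case week-24 t test as a sensitivity analysis.

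The stated endpoint scale and the visit schedule can stay as they are; changing either is a separate question and is not needed here. The cost is a change of wording and a slightly more complex model. No new data are required, and the precision gain is only about 1 to 2% if dropout proves random.
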